## Study Summary

**Design:** Retrospective multi-centre cohort study.

**Participants:** Male and female prisoners, aged 18+, in selected category A-C prisons in England who have been managed by the Assessment, Care in Custody and Teamwork (ACCT) process in response to concerns of being at risk for self-harm or suicide.

**Data sources:** Three linked data sources: ACCT records, SystmOne medical records and Nomis (a central prison database).

**Study period:** Included participants had ACCTs closed prior to June 2022, with a minimum of three months of follow-up per participant.

**Risk factors:** A range of variables including demographics characteristics, variables indicative of mental health at opening and closure of the ACCT, history of self-harm, variables relating to history of and reasons for incarceration, variables indicative of health status and medication use.

**Primary outcome:** ACCT reopening within 3 months following closure of the ACCT. The target sample size was 750, anticipating that a 20% event rate would yield 150 outcome events within 3 months.

**Outputs:** The main objective is to produce models that estimate outcome probabilities within 3 months, with appropriate measures of predictive accuracy.

These models will be used to obtain scoring systems for the calculation of risk to be used prospectively at the time of ACCT closure.

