## 2. Statistical Analysis

Available variables, and the data sources used to collect them, are listed in Appendix 1.

The main statistical analysis method used will be Cox proportional hazards regression for survival analysis, using time to first ACCT reopening following the closure of the index ACCT as the primary outcome and a set of pre-specified candidate predictors (see separate subsection below) as covariates. In the event that the goodness-of-fit of the Cox model is inadequate, other more suitable survival analysis models, including parametric survival models, will be explored.

We will further extend the basic model to allow for possible time-varying effects of risk factors (Thomas and Reyes, 2014, Section 2.3) and/or to allow dynamic prediction using time-varying covariates (Van Houwelingen and Putter, 2012) using the 'dynpred' R package, to allow the risk to be re-estimated at the time of post-ACCT review (which occurs 7 days after closure in older ACCTs and 6 weeks after closure in newer ACCTs). This may require refitting of the model to incorporate data that is available at a second baseline (the post-ACCT review) that was unavailable at the first baseline (closure of the original ACCT).

The primary outcome is self-harm and/or substantially elevated risk or concern of future self harm that leads to a new ACCT being opened, within 3 months following ACCT closure, among prisoners who remained in custody at the time of data collection. Model fitting will be performed using follow-up data within 3 months of follow-up. Risk estimates will use the 3-month event horizon and model performance measures will be calculated in relation to this time point. Risk estimates will also be expressed conditional on the length of the post-ACCT period that has already elapsed, to allow for the likely non-linear decline in risk over time, the initial 30 days after ACCT closure being a particular high-risk period for self-harm. The distribution of risk estimates observed will guide a decision about a probability threshold indicative of high risk, although performance at a range of thresholds will be presented.

Individuals for whom no outcome event has occurred at the time of last follow-up will be considered as right-censored at that time. This includes those who have left prison, for whom the release date is recorded.

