Each individual has an 'index ACCT' that defines the time point at which risk factor variables are available, and the closure of this ACCT is interpreted as time 0 for defining subsequent follow-up times. In the case that more than one ACCT from the same individual is available as an index ACCT, the most recent of these that has substantially complete risk factor data will be used in the primary analysis. A sensitivity analysis will be carried out to check that the selection of this index ACCT does not have an undue influence on results.

Covariates that have more than 30% missing data will be excluded. Missing data on covariates with at most 30% missing data will be imputed via multiple imputation (with twenty imputations) using a regression model that uses other risk factors and the outcome variables as explanatory variables (Sterne et al., 2009). Estimates of coefficients in the final prediction rule will be combined across imputations, using standard methodology (Barnard and Rubin, 1999). It is possible that the variable selection procedure would give different sets of variables in different imputations of the data-set; for this reason, the 'RR' method described by Wood et al. (2008) will be used. In this method,

summary estimates are computed by combining information across all imputed data-sets at each stage as part of a single variable selection process.

Internal validation will be assessed using bootstrapping to assess the predictive accuracy of the model (Harrell et al., 1996). Predictive accuracy will be summarised using several summary measures, including the concordance index (Harrell et al., 1982) and estimates of sensitivity and specificity corresponding to different values of a risk threshold. The proportions of predicted and observed events at different levels of predicted probability will be compared using a calibration plot.

Data will be collected from multiple prison sites (expected to be 6 different prisons in England). The main model will be fitted using data from all sites combined. Performance measures will also be presented stratified by site in order to identify whether there are any major between-site differences that may impact on performance in an external validation sample.

This analysis plan does not incorporate an external validation step as it is planned to conduct a separate external validation substudy, using data from a different selection of prisons, concurrently with the analysis in the model development stage.

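### Where a prisoner has several available ACCTs, indexing on the most recent one selects on the outcome and biases the 3-month risk downward, by an amount the SAP leaves unknown

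*SAP*

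**What the plan says.** SAP section 2 (Statistical Analysis) gives each prisoner one index ACCT, and "the closure of this ACCT is interpreted as time 0 for defining subsequent follow-up times". The model is a Cox regression "using time to first ACCT reopening following the closure of the index ACCT as the primary outcome". The choice of index arises "In the case that more than one ACCT from the same individual is available as an index ACCT"; then "the most recent of these that has substantially complete risk factor data will be used in the primary analysis". On this choice the section adds: "A sensitivity analysis will be carried out to check that the selection of this index ACCT does not have an undue influence on results". It names no alternative rule and no criterion for undue influence.

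The Study Summary sets the frame: "Included participants had ACCTs closed prior to June 2022, with a minimum of three months of follow-up per participant". No start date for the window is given. The expected yield is: "The target sample size was 750, anticipating that a 20% event rate would yield 150 outcome events within 3 months". The product is to be "scoring systems for the calculation of risk to be used prospectively at the time of ACCT closure".

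In Appendix 1, reopening dates come from Nomis, while several risk factors come from the ACCT record itself. An indicator of a previous ACCT in the 6 months before the index opening is a Group 1 variable, so it always stays in the model.

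**The concern.** Suppose closure A is followed by a new ACCT, B. A's outcome is an event. If B also closed before the cut-off, is available and has substantially complete data, the rule indexes B and A leaves the cohort. A is dropped because its own outcome occurred. A closure with no later ACCT cannot be displaced in this way. The cohort therefore loses events faster than non-events.

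Staff who use the score at a closure cannot know whether that ACCT will prove to be the prisoner's last. A model built on closures picked partly for being last will understate the risk at a typical closure. The SAP also lets the distribution of risk estimates guide the high-risk threshold, so a downward shift would carry into classification. The bootstrap and the calibration plot use the same selected cohort. They can show good agreement with a risk that is itself too low.

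**Working it through.** **The plan's own figure.** 750 × 0.20 = 150 events. This reproduces.

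**Direction.** Let p be the true 3-month risk over eligible closures. Let d1 be the chance that a closure with an event is displaced by a later index ACCT, and d0 the same chance for a closure without an event within 3 months. The share of events among retained closures is

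p(1 − d1) / [p(1 − d1) + (1 − p)(1 − d0)],

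which is below p whenever d1 > d0. An event within 3 months guarantees a later ACCT, and no event within 3 months does not, so d1 > d0 unless no repeat ACCT is ever available as an index. As a hand check, take p = 0.20 and d0 = 0, so that the share is 0.20(1 − d1)/(1 − 0.20·d1):

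- d1 = 0.10: 0.18/0.98 = 18.4%
- d1 = 0.25: 0.15/0.95 = 15.8%
- d1 = 0.50: 0.10/0.90 = 11.1%

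**Size by simulation.** The inputs below are assumptions, because the SAP does not give them:

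- 200,000 prisoners, first closure uniform over W months before the cut-off;
- reopening hazard calibrated to a 20% risk at 3 months after the first closure;
- exponential ACCT length with mean 0.3 month;
- one binary predictor with log hazard ratio 0.7;
- each closure available with probability a.

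Results without further between-person heterogeneity (events are 750 × the unrounded share):

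| W (months) | a | Most recent | Earliest | All closures | Events per 750, most recent |
|---|---|---|---|---|---|
| 6 | 0.10 | 19.2% | 20.3% | 20.3% | 144 |
| 6 | 0.25 | 17.4% | 20.3% | 20.5% | 131 |
| 6 | 0.50 | 14.5% | 20.4% | 20.6% | 109 |
| 6 | 1.00 | 7.9% | 20.0% | 20.4% | 59 |
| 12 | 0.10 | 19.5% | 20.7% | 20.9% | 146 |
| 12 | 0.25 | 17.0% | 20.3% | 20.5% | 127 |
| 12 | 0.50 | 13.0% | 20.2% | 20.6% | 97 |
| 12 | 1.00 | 5.4% | 19.8% | 20.5% | 41 |

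A second set of assumptions (Weibull shape 0.7, mean ACCT length about 15 days, no heterogeneity) gave similar figures. With all ACCTs available: 7.2% at 6 months, 4.4% at 12 months and 17.8% for a 1-month window. With 10% available: 18.6% at 6 months and 18.4% at 12. A 1-month window with at most half available gave about 19-20%.

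With gamma heterogeneity between prisoners, the comparison figure itself rises. In the first set at W = 12, a = 1, the most-recent rule gave 7.2%, the earliest closure 19.9% and all closures 25.6%. At W = 12, a = 0.10, they gave 23.5%, 24.9% and 25.8%. In every scenario the most-recent rule was the lowest.

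**Predictor effects (log hazard ratios, most recent against all closures).**

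- Previous ACCT within 6 months, W = 6, with heterogeneity: 1.17 against 0.66 at a = 1 (hazard ratios exp(1.17) = 3.2 and exp(0.66) = 1.9); 0.83 against 0.65 at a = 0.5; 0.70 against 0.67 at a = 0.1.
- The same variable without heterogeneity: 0.47 against 0.00 at a = 1; 0.03 against −0.01 at a = 0.25.
- The ordinary binary predictor, W = 12, no heterogeneity: 0.90 against 0.70 at a = 1; 0.71 against 0.69 at a = 0.5.

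**The case against.** The strongest reply concerns size. The rule acts only on prisoners with more than one available ACCT, and their number is not stated. Reopening dates come from Nomis, so a reopening whose ACCT record was not collected, or that closed after the cut-off, still counts as an event and displaces nothing. If few repeat records were collected, the shortfall is about one to one and a half percentage points. This stands, and it rules out an unconditional statement of large bias.

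Second, the plan foresees a sensitivity analysis on exactly this choice, and a separate external validation in other prisons could expose miscalibration. This stands in part. The sensitivity analysis has no stated alternative and no stated consequence, so as written the score still comes from the primary cohort. The validation runs concurrently, and this SAP gives no index rule for it, so it cannot be counted on to find the problem.

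Third, the alternatives are not equivalent. With heterogeneity, the earliest closure and all closures differ by several points (19.9% against 25.6% above), so one must be chosen to match the intended use. This also stands. A random ACCT per prisoner is no cure, because people with events have more ACCTs. At W = 12, a = 1, without heterogeneity, it gave 13.5%.

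Last, a completeness condition is reasonable for nearly empty records. The term is undefined and imputation is already planned, but this is a secondary matter.

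**Conclusion.** The point holds for its mechanism and direction, both of which follow from the SAP's own definitions. The size is unknown. It lies between about one percentage point and a loss of most of the 150 expected events, depending on the window length and on how many repeat ACCTs are available as index. The simulated range assumes a true risk of 20% and the inputs listed above.

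A reader might infer three stronger things that the SAP does not support:

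- That being the most recent ACCT nearly implies no reopening. This needs near-complete availability of repeat ACCTs, which is nowhere stated.
- That predictor effects are distorted in general. Clear distortion appears mainly for the forced indicator of a previous ACCT when most repeat ACCTs are available; at lower availability the ordinary predictor hardly moved.
- That the finished tool will certainly give staff too low a risk. The authors could still act on the sensitivity analysis or the external validation, although the SAP does not commit them to it.

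The primary rule should still be changed before the model is fitted, because the bias has a known direction and internal validation cannot reveal it.

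**What to change.** - **Primary analysis.** Because the score is meant for any ACCT closure, use all eligible closures, each followed to its own first reopening. Handle variance (including the p-values used in backward selection), bootstrap resampling and imputation at prisoner level.
- **If one closure per prisoner is required.** Use the earliest eligible closure on or after a fixed calendar date, and state that this targets risk after the first closure in the window.
- **Sensitivity analysis.** Keep the most-recent rule here, and state in advance which results will be compared and what difference would count as undue.
- **Reporting.** Give the window's start date, the number of prisoners with several eligible ACCTs, and the number of closures the most-recent rule would displace.
- **Completeness.** Define any criterion in advance and without reference to later ACCTs.

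The cost is SAP wording and a re-run. The planned sensitivity analysis already presumes that the other ACCTs are available. The drawbacks are a clustered analysis and possibly more missing items and more older-version ACCT documents, whose post-closure review is at 7 days rather than 6 weeks.

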| First reception at current prison                              | Nomis  | -     | Date                    | Used to calculate time between reception at current prison and ACCT opening (see below)                                                                                   |
| Follow-up ACCT reopening                                       | Nomis  | -     | Date                    | Primary outcome is time between ACCT closure and first subsequent ACCT reopening                                                                                          |
|                                                                |        |       |                         |                                                                                                                                                                           |
| Risk factor variables                                   |        |       |                         |                                                                                                                                                                           |
| Sex                                                            | -      | 1     | Binary                  | Prisons are single-sex so prison site indicates sex of prisoner. Coded as Male or Female.                                                                                 |
| Reason for ACCT opening                                        | ACCT   | 1     | Categorical             | Categorised as self-harm; threat of self-harm; low mood (including all other reasons for ACCT opening)                                                                    |
| Method of self-harm                                            | ACCT   | 2     | Categorical             | Categorised as cutting; strangulation; overdose; other method; not applicable (no self-harm)                                                                              |
| Current suicidal thoughts or intentions                        | ACCT   | 1     | Binary                  | At ACCT opening. Categorised as Yes or No.                                                                                                                                |

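### The imputation model omits prison site, although performance is then compared by site; gaps concentrated in one prison can create or hide site differences

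*SAP*

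**What the plan says.** Section 2 of the SAP sets the missing-data rules. "Covariates that have more than 30% missing data will be excluded"; covariates at or below that limit are multiply imputed, with twenty imputations, "using a regression model that uses other risk factors and the outcome variables as explanatory variables". The limit is stated per covariate, with no limit within a prison.

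The same section expects six prisons and states that "The main model will be fitted using data from all sites combined". It adds: "Performance measures will also be presented stratified by site in order to identify whether there are any major between-site differences", because such differences could affect performance in the external validation sample.

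The risk factor table in Appendix 1 does not list prison site. The only link is the note on sex: "Prisons are single-sex so prison site indicates sex of prisoner". Nothing else in the SAP adds site as an auxiliary variable or imputes within site.

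**The concern.** An imputation model should carry the structure of the analyses run on the completed data. Here it does not. Imputing from the other risk factors and the outcome assumes that, given those variables, a missing value follows the same distribution in every prison. Sex separates men's from women's prisons but cannot separate two prisons of the same sex. The plan therefore partly assumes away the between-site variation that it then sets out to look for.

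If one prison lacks many values of a covariate that is more common there, the imputed values pull that prison towards the pooled distribution. Its predicted risks become too low, and it looks miscalibrated when it is not. If its true risk is lower than the model implies, the same pull can hide that. The comparison at stake is the one meant to warn of trouble in external validation.

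**Working it through.** **The plan's own figures.** "The target sample size was 750" with a 20% event rate (Study Summary): 750 × 0.20 = 150 events, as stated. With six prisons, taken as equal in size (an assumption): 750/6 = 125 prisoners and 150/6 = 25 events per prison.

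**Does the 30% rule protect?**
- Wholly missing at one of six equal prisons: 1/6 = 16.7% overall. Kept, and imputed entirely from the other five.
- Wholly missing at two: 2/6 = 33.3%. Excluded.
- 80% missing at one and 5% at the other five: (5 × 5% + 80%)/6 = 17.5%. Kept.

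**Size of the effect.** The SAP gives no missingness or prevalence by prison, so all such inputs below are assumptions. Every simulation uses six prisons of 125, about 20% events, and a logistic outcome in place of 3-month Cox risk. O/E is observed over expected events at the affected prison.

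*Simulation 1.* One binary predictor, prevalence 0.20 to 0.70 by prison; 80% missing at the 0.70 prison, 5% elsewhere; no true site effect; 600 data-sets, 10 imputations.
- Imputed prevalence at that prison: 0.43 without site, 0.69-0.70 with site (truth 0.70).
- O/E: 1.13 (odds ratio 2) or 1.18 (odds ratio 3) without site; 1.01 with site.
- Pooled odds ratio: 1.98 versus 1.97.

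*Simulation 2.* One binary predictor (odds ratio 2.5) and one continuous covariate; prevalence 0.30 at the other five prisons; gaps only in prison A; 150 data-sets, 8 imputations.

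| Prevalence in A | Missing in A | True site effect (log-odds) | O/E full data | O/E without site | O/E with site |
|---|---|---|---|---|---|
| 0.30 | 80% | none | 0.97 | 0.97 | 0.97 |
| 0.50 | 80% | none | 1.01 | 1.10 | 1.02 |
| 0.70 | 50% | none | 1.00 | 1.09 | 1.00 |
| 0.70 | 80% | none | 1.00 | 1.17 | 1.01 |
| 0.70 | 80% | -0.35 | 0.81 | 0.94 | 0.81 |
| 0.70 | 100% | none | 0.98 | 1.21 | 1.21 |

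Row 1: no distortion when prevalence is equal. Row 5: a real difference is largely hidden. Row 6: a site term cannot help when nothing is observed at that prison. The site c-index moved by at most about 0.025. With no true site effect the pooled log odds ratio hardly moved (0.902 full data, 0.903 without site, in row 4). In row 5 it was 0.844 with full data, 0.906 without site and 0.843 with site.

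*Simulation 3.* Sensitivity and specificity at an assumed 25% risk threshold; prevalence 0.70 at one prison, 0.30 elsewhere; odds ratio 2.5; 200 data-sets. With 80% missing at that prison and 5% elsewhere, its sensitivity was 0.62 (full data), 0.47 (without site) and 0.60 (with site); its specificity was 0.62, 0.76 and 0.63. With 50% missing, sensitivity was 0.61, 0.54 and 0.62.

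*Milder inputs.* Prevalence 0.50 at the affected prison, 0.35 elsewhere; 300 data-sets, 5 imputations.

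| Missing at that prison | Odds ratio | O/E without site | O/E with site | Difference |
|---|---|---|---|---|
| 20% | 2 | 1.00 | 0.99 | 0.01 |
| 20% | 3 | 1.03 | 1.01 | 0.02 |
| 40% | 2 | 1.03 | 1.01 | 0.02 |
| 40% | 3 | 1.04 | 1.00 | 0.04 |

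A repeat with 1,500 data-sets, 20 imputations and 5% missing elsewhere gave differences of 0.011, 0.017, 0.023 and 0.035 in the same order. Repeating simulation 1 with prevalences evenly spaced (0.20, 0.30, ..., 0.70; 600 data-sets, 20 imputations) gave 1.10 and 1.14 without site and 1.00 with it, so the adverse figure depends somewhat on the other prisons' prevalences.

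**The case against.** The strongest reply is that the harm is conditional and may be small. It needs gaps concentrated in one prison and a covariate that differs there after conditioning on the other risk factors and the outcome. The SAP shows neither. Ten of the listed risk factors come from Nomis, which the Study Summary calls a central database, so site-specific record keeping is least plausible for those. Where a prisoner has several eligible ACCTs, the SAP takes the most recent with substantially complete risk factor data, which limits gaps somewhat. This stands: the claim must be that the omission *can* distort.

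Second, noise. In the simulations the standard deviation of one prison's O/E with full data was about 0.13-0.15, so even an adverse shift of 0.12-0.17 is about one standard deviation. The site comparison is descriptive, seeks only major differences, and is followed by a separate external validation. This also stands and limits the priority. It does not excuse a systematic error that is almost free to remove.

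A reader might go further and infer that the site comparison will be wrong, that the prediction model is compromised, or that records are kept differently in each prison. The SAP supports none of these. It reports no missingness by site and does not describe how records are kept locally, and the simulated pooled coefficients hardly moved when there was no true site effect. Nor has it been shown that shifts from several covariates add up; they could cancel.

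**Conclusion.** The point holds in conditional form. The SAP fixes an imputation model without site and then uses the imputed data to compare sites, and its 30% rule does not screen out gaps confined to one prison.

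If missingness is concentrated in a prison where the covariate's distribution differs, that prison's O/E can be shifted by roughly 0.1 to 0.2 in adverse cases, and by about 0.01-0.04 with 20-40% missing and a modest prevalence difference. The shift can create a false difference or mask a true one, and it reaches sensitivity and specificity at a threshold as well as calibration. It affects the c-index far less. With about 25 events per prison, site results are imprecise either way.

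These sizes rest on assumed prevalences, odds ratios, missingness patterns and equal sites, and on a logistic stand-in for the Cox model. The main prediction model is not called into question.

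**What to change.** In the missing-data paragraph of section 2, state that the imputation models also include prison site as a categorical auxiliary variable. Let it replace sex there: site determines sex, so the two together are exactly collinear. Sex stays in the prediction model as a Group 1 variable. Site is not added to the prediction model, so the tool can still be used in other prisons.

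Keep the 30% rule as it is, and report covariate missingness by site beside it. Where a covariate is wholly missing at a prison, a site term cannot help. Leave that prison out of the site-specific performance of any model using that covariate, or flag its results.

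Cost: a sentence or two of SAP text, one table, and four to five extra terms per imputation regression (five indicators for six prisons, less the sex term they replace). No new data are needed.

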## **Risk factors**

Risk factors will be considered in two groups, of differing levels of priority. The 'List of risk factor variables' table in the Appendix specifies the group to which each variable is assigned.

Group 1 consists of variables that will be included in the statistical model regardless of statistical significance. These include demographic characteristics that it is necessary to include to ensure the model has face validity, and other risk factors suspected on the basis of previous research or subject-matter judgment to be associated with a self-harm outcome.

Group 2 consists of variables likely to show an association with outcomes but which are not required to be included to achieve face validity. The model will use a backwards stepwise selection procedure to determine whether to retain these variables in the model, with Group 1 variables always retained and Group 2 variables sequentially rejected in order of p-value until no group 2 variables remain that have p-values greater than 0.1.

This strategy of risk factor adjustment recognises that the final model must demonstrate face validity, whilst simultaneously allowing the inclusion of additional risk factors if they show an association with outcome variables. The variables are considered in two groups in this way to recognise that a parsimonious model is preferable and easier to use in practice, provided that it has acceptable predictive ability.

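### By-site performance is judged by a model fitted to each prison's own data, so it understates the site differences it is meant to flag, most of all at a women's prison; leave-one-prison-out validation is a cheap improvement

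*SAP*

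**What the plan says.** SAP section 2 describes the setting: "Data will be collected from multiple prison sites (expected to be 6 different prisons in England". On the fit it says "The main model will be fitted using data from all sites combined". It names no site term, site stratum, frailty or clustered variance. On the check it says "Performance measures will also be presented stratified by site in order to identify whether there are any major between-site differences", and it gives the reason: such differences could affect how the model performs in an external sample.

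Other validation is described in the same section. "Internal validation will be assessed using bootstrapping to assess the predictive accuracy of the model"; the unit to be resampled (prisoner or prison) is not stated. External validation is left to a separate substudy, "using data from a different selection of prisons, concurrently with the analysis in the model development stage".

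Appendix 1 places sex in Group 1 and notes "Prisons are single-sex so prison site indicates sex of prisoner". Under Risk factors, "Group 1 consists of variables that will be included in the statistical model regardless of statistical significance". Sex is therefore always in the model and takes a single value within each prison. The SAP does not say how many of the prisons hold women.

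**The concern.** The by-site table is the SAP's only look at differences between prisons, and its purpose is to warn about new ones. A prison that helped to set the baseline hazard and coefficients pulls the predictions towards its own event rate, so its apparent miscalibration shrinks. The forced sex term makes this worse. Because it is constant within prison, it sets a separate overall level for women's prisons, and each prison is in effect compared only with prisons of its own sex, itself included.

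The output is a scoring system for use when an ACCT is closed. If one prison's reopening rate is unusual, the table may not show it, and a women's prison is where it is least likely to show.

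**Working it through.** **Inputs from the SAP.** Study Summary: "The target sample size was 750, anticipating that a 20% event rate would yield 150 outcome events within 3 months". Section 2: six prisons expected. Check: 750 × 0.20 = 150 events, which reproduces the stated figure.

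**Assumptions, not in the SAP.** Six equal prisons, so 750/6 = 125 prisoners and 150/6 = 25 events each. One to three women's prisons. Between-prison SD of the log hazard (τ) of 0.1 to 0.5. A c-index of 0.65 to 0.75.

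**1. How much own-site evaluation hides.** Let dᵢ be prison i's log event rate, and let m equal prisons share one fitted level. On that scale, approximately:

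- own-site departure = dᵢ − mean of all m
- left-out departure = dᵢ − mean of the other m − 1
- own-site = (m − 1)/m × left-out

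Results:

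- m = 6 (sex set aside): 5/6 is kept and 1/6 hidden.
- m = 2 (a women's prison when there are two): 1/2 is hidden.
- m = 1 (the only women's prison): everything is hidden.
- For men's prisons with sex in the model, m = 5 hides 1/5 and m = 4 hides 1/4.

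The case m = 1 also follows from the Cox score equation for a 0/1 covariate. Summed over women, observed events minus fitted cumulative hazard equals zero. If all the women are in one prison, its observed/expected ratio (O/E) is 1 on that scale whatever its true departure, and it will be close to 1 for three-month predicted risks.

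A simulation (4,000 replicates, six prisons of 125, 20% baseline risk, event counts only) gives the root mean square of log(O/E):

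| τ | Own-site | Left-out | Ratio | Women's site, two such: own | Left-out | Ratio |
|---|---|---|---|---|---|---|
| 0.2 | 0.233 | 0.278 | 0.84 | 0.184 | 0.367 | 0.50 |
| 0.3 | 0.303 | 0.360 | 0.84 | 0.233 | 0.457 | 0.51 |
| 0.5 | 0.446 | 0.527 | 0.85 | 0.355 | 0.680 | 0.52 |

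The first block leaves out the sex term. The ratios barely depend on τ. They concern overall calibration, not discrimination.

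**2. The bootstrap.** If prisoners are the resampling unit, the chance that a given prison is absent from a resample is (5/6)^750, effectively zero. Such a bootstrap never tests an unseen prison.

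**3. Precision per prison.**

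- SE of ln(O/E) = √((1 − 0.2)/25) = 0.179, so an O/E of 1 has a 95% interval of about 0.70 to 1.42.
- The c-index has a 95% half-width of about 0.12 to 0.13 per prison (Hanley–McNeil, 25 events and 100 non-events), against about 0.05 pooled.

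**4. The sex coefficient, for illustration only.** With k women's prisons:

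- model-based variance = 1/(25k) + 1/(25(6 − k)) = (1/25) × (1/k + 1/(6 − k))
- added between-prison variance = τ² × (1/k + 1/(6 − k))
- SE ratio = √(1 + 25τ²), whatever k is

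This gives 1.12, 1.41, 1.80 and 2.24 for τ = 0.1, 0.2, 0.3 and 0.4. With k = 1 and τ = 0.3, the SE goes from √0.048 = 0.22 to √(0.048 + 0.108) = 0.39.

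**The case against.** The strongest reply is that the SAP asks little of this table. It is to flag major differences, and performance in new prisons is assigned to a substudy in other prisons. The pooled model has no site terms, so site differences are not fitted away, and five sixths of the signal survives. That stands, and it is why this is an improvement and not the repair of an invalid analysis. It does not dispose of the point. The table's stated purpose looks ahead to external performance, the substudy runs alongside development and does not correct the table, and the loss at a women's prison is a half or more.

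A reader might infer that neither the by-site check nor the sex effect can be trusted for a new prison. The SAP does not support that:

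- The check keeps most of the overall signal.
- Forcing sex in is not a fault. Single-sex prisons make the overlap with site unavoidable, and for prediction sex may legitimately stand in for prison type.
- The standard error of sex decides nothing planned. The term stays in regardless of significance, and the score uses the point estimate.
- The SE ratio depends wholly on an assumed τ; at 0.1 it is only 1.12.
- Nothing in the SAP shows that the sex points reflect one prison's reopening habits.

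Two objections to the remedy also stand. With a single women's prison, holding it out leaves only men, so sex cannot be estimated and the held-out women cannot be scored by the full model. And six clusters barely identify a frailty variance, so a site frailty cannot be the main answer.

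**Conclusion.** The point holds as a cheap improvement. The by-site table understates between-prison differences in overall calibration by about one sixth with six equal prisons and sex set aside, by about half at a women's prison if there are two, and completely if there is one. These fractions rest on equal site sizes and six prisons. They hardly depend on how much prisons really differ, but the absolute miscalibration hidden does, and the SAP gives no figure for that.

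The table remains useful as description. The sex coefficient cannot be separated from prison, and its model-based interval leaves out variation between prisons. That calls for a stated limitation, not a change to which variables are forced in.

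**What to change.** In SAP section 2:

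- Keep the by-site table and label it descriptive.
- Add internal-external (leave-one-prison-out) validation. For each prison, repeat imputation and backward selection on the other prisons and apply the resulting model to the held-out one. Report held-out c-index, O/E and calibration slope per prison and pooled.
- State the bootstrap resampling unit.
- Report the number of prisons and events by sex.
- State that the sex coefficient cannot be separated from prison and that its model-based interval omits between-prison variation.
- If there is only one women's prison, say that sex is not estimable when it is held out, and limit the leave-one-out check to the men's prisons.
- Treat a site frailty as a sensitivity analysis at most.

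Cost: about six refits of the whole procedure on data already held, and a few sentences of SAP text. The downside is wide per-prison intervals at about 25 events each, so the held-out results should be read mainly as a pooled summary with its spread.
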